### Design

This study is a single-blind multicentre randomized controlled trial (RCT) with two conditions: 1) VRcbt for paranoid delusions as experimental condition, and 2) CBTp for paranoid delusions as active control condition. Participants in both conditions may receive other types of treatment as usual, including antipsychotic medication, with the exception of CBT. The effects of the two conditions are compared at baseline (*T*_0_), at post-treatment (*T*_1_), and at three month follow-up (*T*_2_). A Consolidated Standards of Reporting Trials (CONSORT) inclusion flow diagram is shown in Fig. 1.

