### Interventions

#### VRcbt

VRcbt will be delivered by trained therapists, with at least a postgraduate qualification in CBT, and with a minimum of half a year of experience in psychosis treatment.

VRcbt consists of maximum 16 sessions within an 8–12-week time-frame. Sessions will last maximum 75 min, of which 40 min are spent in virtual social situations that trigger paranoid delusions and distress. The remaining time will be used to plan and reflect on exercises and to complete the session measurements. Throughout the first sessions, therapists construct individually tailored case-formulations based on CBTp, in close collaboration with the patient in order to create a shared understanding of the current paranoid ideas, related feelings and behaviour. Subsequently, patients are guided by therapists who help them drop safety behaviours and test their paranoid beliefs. The following animated virtual social environments can be used, i.e., café, shopping street, supermarket, bus ride, office and living room. The level of difficulty of the particular social environment can be modified by adjusting the number, gender and ethnic appearance of virtual characters (avatars) present in the situation. The level of hostility and suspicious behaviour can be modified as well. Personalized interactive scenarios can be role-played. The therapist talks via a microphone (with voice distortion) as an avatar and operates the avatars’ body movements. Patients wear an Oculus Rift head-mounted display and navigate through the virtual environments using a controller.

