#### Procedure

Patients who might be eligible for participation will be contacted by their treating clinician and asked if they are interested in participating in the study. Clinicians will ask consent for sharing their contact information with the researchers after which interested patients will be informed about the study and screened by the researchers. After receiving written information about the study, patients will be given a consideration period of one week. If patients decide to participate after one week of consideration, written informed consent will be obtained first, and subsequently patients will complete the GPTS. If the GPTS score is > 40, patients are eligible for the study and the baseline assessment (T_0_) will continue. Following the baseline assessment, the baseline period of EMA will take place. After a week, patients are randomized to either VRcbt or CBTp. Patients allocated to either VRcbt or CBTp, will start with treatment. At the beginning of each session, participants complete the SDS and VAS. At the end of each session therapists complete the CGI. After the treatment period, a post-treatment (T_1_) takes place, followed by a seven days EMA. Finally, a follow-up (T_2_) assessment will be conducted six months after the start of treatment, followed by a final week of EMA. Patients who discontinue participation in the study at an early stage are requested to continue to participate in the measurements.

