#### Data analysis

Analysis will be performed according to the intention to treat principle. The groups will be compared at baseline. In case of baseline differences, variables will be added to further analyses as covariates. Potential covariates include age, sex, duration of illness and medication. The effect of VRcbt will be analysed by random intercept mixed effects regression models. The fixed effect of interaction between treatment group (VRcbt or CBTp) and time on momentary paranoia will be fitted as an estimate of the VRcbt treatment effect. Mean scores before and after treatment on each of the dependent variables will be compared between conditions. To determine the number of sessions needed for achieving clinically meaningful change, scores of patients on the VAS, the SDS and the GCI will be compared between conditions. The standard error of measurement (SEM) will be used to determine the proportion of participants with clinically meaningful change in each condition at each time point. Furthermore, cost-effectiveness analyses (CEA) will be conducted using the TiC-P and the EQ-5D-5L questionnaire. The economic evaluation consists of a CEA with improved momentary paranoia in daily life situations and a cost-utility analysis (CUA) with quality-adjusted life years (QALYs) gained as outcome. For both analyses, the incremental cost-effectiveness ratio (ICER) will be calculated as the between-group cost difference divided by the between-group effect difference. The ICER represents the additional costs needed (or saved) for establishing the VRcbt effect. The cost-utility ratio does the same per additional QALY gained. To handle uncertainty in the cost and effect data, nonparametric bootstrapping will be conducted to simulate 2500 ICERs.

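### Covariate adjustment depends on an observed baseline difference and names neither EQ-5D-5L utility nor costs, so the QALY difference in the ICER may go unadjusted and lose precision

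*Protocol article*

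**What the plan says.** All the relevant statements are in the Data analysis section of the protocol article unless another section is named.

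- The economic evaluation includes "a cost-utility analysis (CUA) with quality-adjusted life years (QALYs) gained as outcome", based on the EQ-5D-5L.
- For both economic analyses, "the incremental cost-effectiveness ratio (ICER) will be calculated as the between-group cost difference divided by the between-group effect difference".
- Uncertainty is handled by resampling: "nonparametric bootstrapping will be conducted to simulate 2500 ICERs".
- Covariates enter under a condition stated earlier in the same paragraph: "In case of baseline differences, variables will be added to further analyses as covariates". The examples are open-ended: "Potential covariates include age, sex, duration of illness and medication".
- On timing, the Design section says "The effects of the two conditions are compared at baseline", and then at T1 and T2. Under VRcbt, "VRcbt consists of maximum 16 sessions within an 8–12-week time-frame", which places T1 at about two to three months. Under Procedure, "a follow-up (T_2_) assessment will be conducted six months after the start of treatment".

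The article does not say how QALYs are built from the EQ-5D-5L. It does not say whether the cost and effect differences are adjusted, or whether the covariate rule extends to the economic evaluation.

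**The concern.** A QALY total is usually the area under the utility curve from T0 onwards. It then contains the utility measured before randomisation, and the later utilities are correlated with that value. If the arms differ by chance at T0, part of the difference appears as QALYs gained or lost.

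The covariate rule is weak protection. It acts only once a difference has been noticed, gives no threshold, and does not list utility or costs among its examples. It also lets the observed data choose the analysis model. The bootstrap does not remove the problem: the imbalance varies between replicates, but around the value observed in the trial.

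Cost-effectiveness is part of the stated hypothesis (Objectives; Discussion). Both arms are active therapies and the horizon is about six months, so the QALY difference may well be small. A modest shift could then change its sign and the quadrant of the ICER.

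**Working it through.** **The plan's own figures.** The article gives no figure for QALY variance, utility correlation or precision of the ICER, so there is nothing to reproduce. The sample-size section concerns momentary paranoia and supplies only the number of patients: 106 at 1:1, or 53 per arm. With the stated 15% drop-out this is about 0.85 × 53 = 45 per arm.

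**Assumptions, none of them in the article.** QALYs by the trapezoid rule over 0.5 years; EQ-5D-5L at T0, T1 and T2; T1 between 8 weeks and 3 months; equal utility SD *s* at each visit; one correlation ρ between any two visits, from 0.3 to 0.8; *s* from 0.2 to 0.3.

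**Formulas.** With T1 at time t (in years), QALY = (t/2)·u0 + 0.25·u1 + ((0.5 − t)/2)·u2.

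- Slope on baseline utility: b = w0 + ρ(w1 + w2).
- QALY variance: V·s², where V = Σw² + 2ρΣw_i·w_j.
- Share of QALY variance removed by adjusting for u0: R² = b²/V.

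**Worked case: T1 at 3 months, ρ = 0.5.** The weights are 0.125, 0.25 and 0.125.

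- b = 0.125 + 0.5 × 0.375 = 0.3125.
- V = 0.09375 + 2 × 0.5 × 0.078125 = 0.1719.
- R² = 0.3125²/0.1719 = 0.568.

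**Range.**

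| T1 | ρ | slope b | R² | adjusted SE / unadjusted SE |
|---|---|---|---|---|
| 8 weeks | 0.3 | 0.204 | 0.289 | 0.843 |
| 8 weeks | 0.5 | 0.288 | 0.478 | 0.723 |
| 8 weeks | 0.8 | 0.415 | 0.785 | 0.463 |
| 3 months | 0.3 | 0.238 | 0.401 | 0.774 |
| 3 months | 0.5 | 0.3125 | 0.568 | 0.657 |
| 3 months | 0.8 | 0.425 | 0.826 | 0.417 |

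**Size in QALYs (T1 at 3 months, ρ = 0.5, s = 0.25, 53 per arm).**

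- SE of the baseline difference: 0.25 × √(2/53) = 0.0486.
- Shift in the QALY difference from a one-SE imbalance: 0.3125 × 0.0486 = 0.0152.
- Unadjusted SE of the QALY difference: 0.25 × √0.1719 × √(2/53) = 0.0201. Adjusted: 0.0201 × 0.657 = 0.0132.
- For s from 0.2 to 0.3, the one-SE shift runs from 0.012 to 0.018. With 45 per arm and s = 0.25 it is 0.0165.

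**What the conditional rule could let through.** No threshold is stated. If the trigger were a 5% test, imbalances of up to 1.96 SE would go unadjusted, a shift of up to 1.96 × 0.0152 = 0.030 QALY.

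**The other construction.** If QALYs gained means change from baseline (area minus 0.5·u0), then at ρ = 0.5 with T1 at 3 months:

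- b = 0.3125 − 0.5 = −0.1875, the weights become −0.375, 0.25 and 0.125, and V = 0.1094.
- R² = 0.1875²/0.1094 = 0.32.

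The shift reverses sign. R² runs from about 0.45 at ρ = 0.3 down to 0.13 at ρ = 0.8. Adjustment still helps, though by less.

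**Net benefit.** Suppose QALYs supply 10% to 75% of net-benefit variance and costs are unrelated to both QALYs and baseline utility. With T1 at 3 months and ρ from 0.3 to 0.7 (R² 0.40 to 0.74), adjusting QALYs removes between 0.10 × 0.40 = 4% and 0.75 × 0.74 = 55% of it.

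**The case against.** The strongest reply is that the article nowhere calls the differences raw. The sentence on the ICER is its general definition, and a ratio of two regression coefficients fits it equally well. How QALYs are built and what is done inside the bootstrap are details that an article commonly leaves to the full protocol or analysis plan. The covariate list is open and the rule comes before the economic evaluation in the same paragraph, so it could bring in baseline utility.

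Most of this stands. The article leaves adjustment open and does not exclude it, and silence on QALY construction is not a fault. What remains is the stated rule: adjustment depends on seeing a difference. Even if the rule covers the economic evaluation, it leaves smaller imbalances in the QALY contrast.

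A reader might go further and infer three things that the document does not support.

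- *That the plan gives a biased cost-utility result.* Under randomisation the unadjusted difference is unbiased over repeated trials, and the bootstrap spread already reflects the extra variability. The loss is in precision and in the particular difference realised.
- *That a baseline imbalance passes in full into the QALY difference.* The direct weight of T0 utility is 0.077 to 0.125 and the total slope 0.20 to 0.43 over the range above.
- *That about half the uncertainty in the cost-effectiveness answer is avoidable.* A share near half belongs to the QALY variance alone at correlations of about 0.4 to 0.5. Cost variance dilutes it.

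The argument is also specific to the cost-utility analysis. The effect in the other economic analysis is worded as improvement in momentary paranoia, so the area-under-the-curve reasoning does not reach it.

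**Conclusion.** The point holds as a matter of efficiency and pre-specification. By the article's wording, the QALY difference may go unadjusted for T0 utility, because adjustment is conditional and neither utility nor costs is named. About 29% to 83% of the QALY variance would be removable over correlations of 0.3 to 0.8 and T1 at 8 weeks to 3 months. In the central case, a one-SE baseline imbalance moves the QALY difference by 0.015, about 75% of its unadjusted SE of 0.020.

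These sizes rest on an assumed SD, equal correlations and a trapezoid QALY. They describe the QALY difference, not the ICER, and no power statement for the ICER follows from them. No figure here supports the size of any gain from adjusting costs. That part of the fix is for consistency between numerator and denominator.

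**What to change.** In the Data analysis section, replace the conditional rule for the economic evaluation with the following:

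- In each bootstrap replicate, resample patients within arm and keep each patient's cost and effect together.
- Regress QALYs on arm and T0 EQ-5D-5L utility.
- Regress total costs on arm and T0 TiC-P costs.
- Do both whatever the observed baseline difference.
- Form the cost-utility ICER from the two arm coefficients, and report the unadjusted ratio as a sensitivity analysis.

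If the full analysis plan already says this, a sentence confirming it is enough. The cost is one sentence and two regressions in the bootstrap loop. Both questionnaires are already trial instruments. Provided they are given at T0, as the Design section implies although the text has no schedule by instrument, no new data, visits or patients are needed.

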## Discussion

In a previous RCT, we compared VRcbt for paranoid delusions to a waiting list [15], as a next step, in this study, we compare VRcbt to CBTp, the latter being the golden standard psychological treatment for psychosis. The main goal of this study is to investigate if the the effect of VRcbt on paranoid delusions in daily life social situations is superior to CBTp. We hypothesize that VRcbt is more (cost-) effective than CBTp for treatment of paranoid delusions and improving daily life social functioning of patients with schizophrenia and related psychotic disorders, and that this difference will be maintained at three month follow-up. This study will add emerging data on VR in the treatment of paranoid delusions. The mean effect size of CBTp for paranoid delusions is only small to medium (d = 0.36) [9], which indicates that treatment needs to be improved. VRcbt has the potential to improve the treatment of paranoid delusions and to be more effective than CBTp, because the risk of avoiding and postponing exposure is much lower. Furthermore, VRcbt enables controllability and environment manipulation, an essential element in treatment of psychosis, but difficult to achieve in a clinical context [11]. Consequently, VRcbt might be more efficient than CBTp as the effect of VRcbt may occur within fewer sessions than CBTp. A systematic review reported a range of 1 to 12 sessions of VR exposure for treatments of anxiety [10], but it is unknown how many VRcbt sessions are needed for treatment of paranoid delusions. In a preliminary pilot study of a short VRcbt intervention for paranoid delusions, reductions in delusional conviction and real-world distress were noted after one session, and a large effect size (d = 1.3) has been reported after six sessions [14]. Our previous study concluded that VRcbt for paranoid delusions is an economically viable approach towards improving patients’ health in a cost-effective manner [47]. Remarkably, while VR is proving its value, studies about the cost-effectiveness of treatment of psychosis and treatment of anxiety in Virtual Reality are limited. Due to emerging technological developments, software and hardware costs have only decreased in recent years. Although VRcbt requires costs in terms of software and hardware, the intervention will be cost-effective when it leads to better outcomes in terms of decreased health care costs (i.e. fewer therapy sessions) and reduced costs due to productivity loss. To conclude, this study will throw light on the (cost)-effectiveness of VRcbt for paranoid delusions. If it proves to be more (cost-) effective than CBTp, VRcbt may become the preferred psychological treatment.

## Data Availability

Not applicable.

## Abbreviations

BCSS: Brief Core Schema Scales
CBTp: Cognitive-behavioural therapy for psychosis
CGI: Clinical Global Impressions Scales
CTRS: Cognitive Therapy Rating Scale
DACOBS: Davos Assessment of Cognitive Biases
EMA: Ecological Momentary Assessments
EQ-5D-5L: EuroQol Five Dimensions Five Levels
GPTS: Green Paranoid Thoughts Scale
HMD: Head-Mounted Display
ICER: Incremental Cost-Effectiveness Ratio
IDS-SR: Inventory of Depressive Symptomatology Self-Report
IPSM: Interpersonal Sensitivity Measure
IPQ: Igroup Presence Questionnaire
PSP: Personal and Social Performance Scale
PSWQ: Penn State Worry Questionnaire
PSYRATS: Psychotic Symptom Rating Scales
QALY: Quality Adjusted Life Year
RCT: Randomized controlled trial
REDCap: Research Electronic Data Capture
SBQ: Safety Behaviours Questionnaire
SDS: Sheehan Disability Scale
SEM: Standard error of measurement
SERS-SF: Self Esteem Rating Scale – Short Form
SIAS: Social Interaction Anxiety Scale
Study ID: Study Identity
T0: Baseline
T1: Post-treatment
T2: Follow-up
TAU: Treatment As Usual
TiC-P: Trimbos Institute and Institute of Medical Technology Assessment questionnaire for Costs associated with Psychiatric illness
VAS: Visual Analogue Scales
VGCt: Dutch Association of Behavioural and Cognitive Therapy
VR: Virtual Reality
VRcbt: Virtual Reality Cognitive-behavioral therapy
